## Abstract

**Background:**

The postmenopausal period can represent an opportunity for women to improve their health and well-being. The Active and Healthy Ageing in Women during early postmenopause (AHAWOMEN) study aims to identify the key determinants of an active lifestyle among middle-aged women, with a focus on the stages and the social-cognitive variables outlined in the Health Action Process Approach (HAPA) model, a theoretical framework for understanding health behaviour change. We expected that HAPA factors and processes of intention creation (motivational phase) and action adoption (volitional phase) will be significant predictors of exercise initiation and maintenance, supporting both the HAPA tenets and the efficacy of HAPA-based interventions.

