**Methods/design:**

This study was approved by the authors’ Institutional Review Committee. Postmenopausal women aged between 45 and 65 years will voluntarily participate. The participants will be allocated to one of three groups: Intervention-Initiators (*n* = 100, random allocation), Control-Sedentary (*n* = 100, random allocation) or Control-Active (*n* = 100, non-random allocation). The intervention group will engage in a supervised exercise programme lasting at least 3 months, supplemented with a HAPA-based intervention for behaviour change. The sedentary control group will not receive any intervention to change their physical activity, while the active control group will consist of women who are already regularly adhering to an active lifestyle. Study variables will be measured at baseline and postintervention phases, as well as at 1, 3, 6 and 12-month follow-ups. The predictors of exercise behaviour in the different phases of the behavioural change process will be explored and compared within and between groups throughout the study. These analyses will help identify the factors that determine the adoption of a healthy active behaviour. Additionally, the effectiveness of the model and the intervention for changing active behaviour will be evaluated.

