The HAPA model has been successfully applied to the adoption and maintenance of a wide range of health-related behaviours (see the meta-analysis with meta-analytic structural equation modelling by Zhang et al. [43]) including physical activity and exercise. Gholami et al. [46, 47] synthesised and meta-analysed cross-sectional, longitudinal and experimental/intervention research investigating the main associations between HAPA constructs and physical activity and exercise behaviour. The summary effect sizes generally supported the model’s predicted associations across samples. The meta-analytic study by Zhang et al. [43] has provided further support for the HAPA direct and indirect predictions in the context of physical activity and exercise. Choi et al. [48] meta-analysed cross-sectional and longitudinal studies on active behaviour (excluding experimental/intervention studies), finding a medium overall effect size (0.28) for the impact of HAPA variables on physical activity. This effect size is comparable to that of the combined influence of the main social-cognitive theory-based constructs including self-efficacy, outcome expectations, goals/intention and self-regulation [35]. It is also consistent with the average efficacy of theory-based interventions for promoting an active lifestyle [30] and the most commonly used behaviour change techniques for adopting active behaviours [49] and maintaining them over a 6 to 15 month period [50] in adult and elderly populations. The findings of all these meta-analyses generally support those of similar previous meta-analyses on the associations between social cognitive determinants including intentions, stage-specific self-efficacy beliefs, action and coping planning and active behaviour [35, 51–53]. This information serves as a basis for designing high-quality theory-guided interventions for the promotion of an active lifestyle.

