After enrolment, participants will be assigned to one of three study groups by randomisation and non-randomisation, depending on the study condition. The groups are as follows: 1) Intervention-initiators (participants who will engage in a supervised exercise programme complemented with a HAPA-based intervention, *n* = 100); 2) control-sedentary (non-active women who will maintain their sedentary lifestyle and will not receive any intervention for promoting behavioural change, *n* = 100) and 3) control-active (women with a regular and sustained exercise habit, *n* = 100).

The sample size has been calculated to include 80 participants per group, considering an *alpha* error of 0.05 and a *beta* error of 0.2, for independent groups and continuous variables, i.e. mean comparisons, with estimated mean values based on previously published studies [64, 65, 68], to ensure sufficient statistical power to detect a moderate treatment effect in a clinical study (Clincalc®). To account for potential dropouts, we anticipate a 20% dropout rate, increasing the sample size up to 100 participants per group. 

Figure 1 shows a flow chart of the study participants, including the selection process.

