To address the first research question, exercise behaviour and HAPA constructs of the motivational and volitional phases (primary outcomes) will be compared across different phases (baseline, post-intervention and follow-ups) (H1) and between the different study groups (intervention participants, sedentary controls, active controls) (H2 and H3). Within-group and between-group analyses will be conducted using parametric (e.g., 1-way or 2-way ANOVAs, Student *t* test) or non-parametric tests (e.g., Friedman’s *χ*^*2*^ test and Wilcoxon’s *Z* pair comparisons for related samples, Kruskal–Wallis’ *H* test and Mann–Whitney’s *U* pair comparisons for independent samples). The choice of test will be determined by the compliance with parametric assumptions of normality and homoscedasticity. A calculation of the effect size will be also conducted (e.g., Cohen’s d). Covariates (e.g., age, menopausal symptom burden) will be introduced (e.g., ANCOVAs).

The second research question (H4 and H5) will be addressed using analyses of bivariate associations (e.g., Pearson *r*, Spearman *rho*), multiple linear regression analyses and multilevel clustering analyses to explore the correlates and predictors of outcome variables as well as intraindividual profiles or patterns of associations. Path analyses and analyses of indirect relationships between variables (e.g., mediation, moderation) will allow for a deep understanding of the complex associations between the study variables. Structural equation modelling will allow for testing the fit of data to the model based on HAPA predictions. Covariates will be introduced to control for their confounding effects (e.g., perceived health status). 

In addition, psychometric properties of the measures will be analysed (e.g., Cronbach’s *alpha*, intercorrelations).

A significance level of *p* < 0.05 will be established.

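### The abstract counts significant HAPA predictors of exercise as support for the efficacy of HAPA-based interventions, which does not follow; efficacy should rest on the randomised comparison of exercise that is already planned

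*Protocol article*

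**What the plan says.** The Background paragraph of the abstract expects HAPA factors and processes to be predictors of exercise, in these words: "will be significant predictors of exercise initiation and maintenance, supporting both the HAPA tenets and the efficacy of HAPA-based interventions". One result, significant prediction, is thus said to support two conclusions.

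Other places bear on the second conclusion:

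- **Abstract, Methods/design.** After the predictor analyses it adds: "Additionally, the effectiveness of the model and the intervention for changing active behaviour will be evaluated". It gives no criterion.
- **Aims and hypotheses.** H1 concerns change in HAPA variables within the intervention group. H2 concerns HAPA determinants at baseline. H3 concerns HAPA self-regulatory skills after the intervention. H4 and H5 concern prediction of exercise. None says that exercise will differ between the randomised intervention and sedentary groups.
- **Data management and analyses.** Exercise behaviour is a primary outcome, together with the HAPA constructs. It is compared across phases (H1) and between the three groups (H2 and H3). The predictor work for H4 and H5 uses, among other methods, "multiple linear regression analyses and multilevel clustering analyses to explore the correlates and predictors of outcome variables". The threshold is common to all tests: "A significance level of *p* < 0.05 will be established".
- **Procedures.** Non-active women are randomised to intervention or sedentary control. The active group is not randomised.

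**The concern.** The question behind the predictor analyses is whether women with higher intention, planning or self-efficacy exercise more. The question behind efficacy is whether women assigned to the programme exercise more than women assigned to no programme. The first can be answered yes while the second is answered no.

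The article's own background shows this. It cites a meta-analysis "finding a medium overall effect size (0.28) for the impact of HAPA variables on physical activity", and says that it pooled cross-sectional and longitudinal studies and left out experimental and intervention studies. The association is therefore expected where nobody receives a programme, and finding it again here says nothing about whether this programme works.

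At stake is what the trial may conclude. As worded, the abstract allows predictor results to be cited for efficacy even if exercise is the same in both randomised arms. The inference can also fail the other way: a programme that raised exercise through supervised access, and not through HAPA constructs, need not make any HAPA score a significant predictor.

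**Working it through.** **Inputs from the article**

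- Sample size: "The sample size has been calculated to include 80 participants per group, considering an *alpha* error of 0.05 and a *beta* error of 0.2", with the aim "to ensure sufficient statistical power to detect a moderate treatment effect in a clinical study".
- Dropout: "we anticipate a 20% dropout rate, increasing the sample size up to 100 participants per group".
- Significance level 0.05. Sidedness is not stated; two-sided is assumed.
- Association 0.28. The metric is not stated; both readings are shown below.

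**The plan's own figure.** 80 / (1 − 0.20) = 100 per group, which matches. The base of 80 cannot be rebuilt because no means, SD or standardised difference are given. For orientation, 80 per group gives 80% power at d = (1.960 + 0.842) × √(2/80) = 0.443; d = 0.5 would need 63.

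**How often one predictor is significant when the intervention has no effect on exercise.** By the Fisher z approximation the rate is Φ(atanh(r)·√(n − 3) − 1.96), plus a negligible opposite tail when r is well above 0. With r = 0.28, atanh(r) = 0.2877.

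| Women analysed | atanh(r)·√(n − 3) | Rate |
|---|---|---|
| 80 (one group of completers) | 0.2877 × 8.775 = 2.524 | 71% |
| 160 (both randomised groups, 2 × 80) | 0.2877 × 12.530 = 3.605 | 95% |
| 240 (all three groups, 3 × 80) | 0.2877 × 15.395 = 4.429 | 99% |

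**Other strengths of association at n = 160**

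- r = 0: 5%
- r = 0.10: 24%
- r = 0.20: 72%
- 0.28 read as a standardised mean difference: r = 0.28 / √(0.28² + 4) = 0.139, which gives about 42%

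**Check by simulation** (8,000 runs per setting, 80 per arm, no arm effect on exercise, r = 0.28). One predictor was significant in 94.9% of runs. If the programme raised the HAPA score by 0.5 SD but left exercise unchanged, the rate was 94.0%. So the inference also fails when the programme moves beliefs only.

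**The comparison that does address efficacy.** In the same simulations, a t test of exercise between the two randomised arms was significant in 4.5% to 5.3% of runs over all settings (80 or 100 per arm, r from 0 to 0.28). With 80 per group its power is 80% at d = 0.443 and 88.5% at d = 0.5.

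These rates answer different questions. The 95% is the power to detect an association that truly exists; the 5% is the type I error of the arm comparison. They belong side by side only because the abstract lets the first kind of result stand for the second kind of claim.

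**The case against.** The strongest reply is that the sentence is an expectation in an abstract and sets no test, analysis set or decision. That stands. A reader might infer that the article contains a decision rule which declares efficacy falsely about 95% of the time. The documents do not support this. No such rule is written, and 95% needs one predictor, the two randomised groups pooled, and 0.28 read as a correlation. The article states neither that metric nor that analysis set.

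A reader might also infer that predictor significance is the only route to an efficacy conclusion. That is not supported either. The abstract announces the evaluation of effectiveness as something additional, and the analysis section makes exercise a primary outcome compared between groups. If exercise were the same in both arms, that comparison would be expected to show it.

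A milder reading exists too: the plural, generic phrase about interventions may mean theoretical support for a class of intervention and not a verdict on this programme. This is possible, but the sentence says efficacy, and the trial tests one such intervention.

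What the reply does not remove is the inference itself. The group comparison of exercise is attached to H2 and H3, which concern HAPA constructs, and it spans three groups, one of them not randomised. Nothing in the text says that the randomised difference in exercise is what decides efficacy, while the abstract says that another result supports it.

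**Conclusion.** The inference is wrong as written and should be removed. Significant HAPA predictors can support the HAPA model; they cannot support efficacy, because they can appear with no intervention effect on exercise. This holds for any association that exists without the intervention, so it does not depend on 0.28.

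The size does depend on assumptions. With a two-sided 5% test, one predictor and no arm effect, the rate is about 71% (n = 80), 95% (n = 160) or 99% (n = 240) if 0.28 is a correlation. At n = 160 it is about 42% if 0.28 is a standardised mean difference, and 5% if there is no association.

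The defect is one of stated inference and of linkage between hypotheses and analyses. The design is sound here: the randomised groups and the exercise measurements needed for a valid answer are already in the plan.

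**What to change.** 1. **Abstract, Background:** end the predictor expectation at support for the HAPA tenets and delete the clause on efficacy.
2. **Aims and hypotheses, and Data management and analyses:** state that efficacy for changing active behaviour rests on the planned comparison of exercise behaviour (IPAQ) between the randomised intervention and sedentary groups, adjusted for baseline IPAQ, with women analysed as randomised. State that predictor significance supports the HAPA model only.
3. **Time point:** the sponsor should choose one and pre-specify it. The article does not point to a single right choice.

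This comparison estimates the effect of the programme as offered, supervised exercise included. It does not isolate the HAPA component, and neither does predictor significance, so the wording of the conclusion should reflect that.

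The cost is a few sentences. No new data are needed, since the IPAQ is taken at every assessment. The small downside is that predictor significance can no longer be cited as evidence of efficacy.

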**Methods/design:**

This study was approved by the authors’ Institutional Review Committee. Postmenopausal women aged between 45 and 65 years will voluntarily participate. The participants will be allocated to one of three groups: Intervention-Initiators (*n* = 100, random allocation), Control-Sedentary (*n* = 100, random allocation) or Control-Active (*n* = 100, non-random allocation). The intervention group will engage in a supervised exercise programme lasting at least 3 months, supplemented with a HAPA-based intervention for behaviour change. The sedentary control group will not receive any intervention to change their physical activity, while the active control group will consist of women who are already regularly adhering to an active lifestyle. Study variables will be measured at baseline and postintervention phases, as well as at 1, 3, 6 and 12-month follow-ups. The predictors of exercise behaviour in the different phases of the behavioural change process will be explored and compared within and between groups throughout the study. These analyses will help identify the factors that determine the adoption of a healthy active behaviour. Additionally, the effectiveness of the model and the intervention for changing active behaviour will be evaluated.

**Discussion:**

This paper describes the rationale, development and methods used in the AHAWOMEN project. Supporting women who intend to become active can help them to translate their goals into sustainable action. Verifying that the HAPA predictions are applicable to postmenopausal women’s adoption of exercise would provide the basis for designing effective interventions for promoting healthy and active ageing that are also tailored to the experiences of middle-aged women.

**Trial registration:**

ISRCTN16251361. Registration date: 01/06/2023 (retrospectively registered).

## Background

### Ageing, postmenopause, health and lifestyle

In a world faced with the social and public health challenges associated with increased life expectancy, the adoption of a healthy lifestyle has emerged as an essential behavioural resource for promoting and protecting health, enhancing quality of life, preventing and managing illness and addressing the challenges of the ageing process. Lifestyle choices and inequalities in health and disease processes are considered key factors in shaping global health [1]. Thus, it is imperative to prioritise interventions offering appropriate responses to these challenges.

Engaging in regular exercise is essential for middle-aged women to maintain good physical health, improve mental health and overall well-being, increase fitness and quality of life and reduce the risk of chronic diseases related to both ageing and lifestyle such as obesity, cardiovascular diseases, Type 2 diabetes and certain types of cancer [2]. Moreover, exercise has a clear positive impact in terms of psychological and social health outcomes [3]. It is recommended that adults engage in at least 150 min of moderate-intensity aerobic exercise or 75 min of vigorous-intensity aerobic exercise each week, or an equivalent combination of moderate- and vigorous-intensity activity [4]. For maximising health benefits, the international recommendations stress the importance of combining aerobic exercise with muscle-strengthening activities at least two days per week. This will promote cardiovascular and metabolic health, boost immunity and improve muscle strength and bone density as well as other fitness qualities such as balance, flexibility and coordination. Additionally, alternating between aerobic and resistance training can help prevent overuse injuries and provide a balanced exercise routine. These guidelines also emphasise the importance of incorporating physical activity into the daily routine (e.g., using active transportation) and adhering to a planned exercise programme [5]. Organisations such as WHO recommend at least 600 MET minutes per week to attain health benefits, which represents the metabolic rate while physically working reaching the recommended physical activity levels, relative to the resting metabolic rate [5]. These figures fall considerably short of the recommended levels suggested by recent research. Specifically, a minimum of 1200 MET-min/week is now suggested to prevent risk of chronic conditions in adulthood [6] or even higher, that is, ≥ 3000–4000 MET-min/week for individuals to be considered as “moderately active” and ≥ 8000 MET-min/week for “highly active” individuals [7]. Consequently, while daily physical activity is beneficial for health, it is not enough for achieving increased health benefits and should be complemented with moderate-to-vigorous exercise.

Abundant evidence suggests that an insufficient percentage of adults meet the recommendations for a healthy active behaviour, which is more evident as age progresses, especially among women. Despite the benefits of an active lifestyle, women at menopausal age and beyond consistently show the lowest adherence to the recommended levels of physical activity [2]. Specifically, in the southern regions of Spain, some studies estimate that only two-thirds of middle-aged and older postmenopausal women engage in at least 300 min per week of healthy physical activity [8] whereas others report that the total weekly time spent performing moderate-to-vigorous physical activity is 195 min, which is less than 30 min per day [9]. A recent study conducted in Spain, using a representative sample from the general population, suggests that 36% of adults perform < 150 min/week of moderate physical activity, 65% < 75 min/week of vigorous physical activity and 27% did not perform any physical activity at all. Moreover, the study revealed significant differences according to gender (e.g., women perform less vigorous exercise and engage in more moderate activity compared to men) and age, with adult women showing the lowest compliance with international recommendations for vigorous exercise. Moreover, 79% of adult women aged 50–64 years do not comply with recommended levels of vigorous exercise and 75% do not engage in any level of vigorous exercise. However, the statistics show a different picture when light or moderate intensity activity is considered [10]. According to the most recent Spanish National Health Survey in 2018 [11], only 16% of adult women in and after the midlife stage meet the recommended levels of activity necessary for good health.

Therefore, middle-aged women, who experience a multitude of biological, psychological and social changes in their life trajectories when transitioning to or after menopause, while simultaneously navigating the ageing process, represent an important target group for active lifestyle promotion policies. Encouraging an active lifestyle during middle age can have long-lasting effects into older adulthood and provide multi-level benefits to women’s quality of life, beyond the management of menopausal manifestations [12–20]. Such benefits extend to other aspects, including improved functional capacity, cardiovascular and metabolic health, bone mineral density, emotional well-being, sexual functioning, sleep quality and cognitive functioning. An active lifestyle is suggested as a strategy for managing the primary health concerns faced by women during adulthood and older age [21]. However, despite its benefits, exercise is not consistently recommended in clinical practice to middle-aged and older women [22]. Moreover, women encounter difficulties in incorporating regular exercise into their routines due to their multi-tasking, multi-role lifestyles, as well as the socio-spatial processes implicated in physical activities, that are often shaped by gender norms and expectations [23–26]. In addition, those more negatively impacted by midlife-related changes are more likely to engage in unhealthier lifestyles that are maintained over time [27, 28].

